### Study duration

13 weeks per study participant

### Withdrawal and replacement of subjects

Criteria for withdrawal

Subjects may prematurely discontinue from the study at any time. Premature discontinuation from the study is to be understood when the subject did not undergo EOS examination and / or all pivotal assessments during the study, i.e. three complete dosage-time profiles.

Subjects must be withdrawn under the following circumstances:

- at their own request
- if the investigator feels it would not be in the best interest of the subject to continue
- if the subject violates conditions laid out in the consent form / information sheet or disregards instructions by the study personal

In all cases, the reason why subjects are withdrawn must be recorded in detail in the CRF and in the subject’s medical records. Should the study be discontinued prematurely, all study materials (complete, partially completed and empty CRFs) will be retained.

Follow-up of patients withdrawn from the study

In case of premature discontinuation after study drug intake, the investigations scheduled for the EOS visit will be performed 7±3 days after study drug discontinuation. The subjects will be advised that participation in these investigations is voluntary. Furthermore, they may request that from the time point of withdrawal no more data will be recorded and that all biological samples collected in the course of the study will be destroyed.

Replacement policy

All renal transplant recipients with HCV-infection, who are considered eligible for the participation in the present trial and who have given written informed consent, will be included in the present trial. Statistical analyses will include an intention-to-treat- and a per-protocol-set.

### Premature termination of the study

The sponsor has the right to close this study at any time. The IEC and the competent regulatory authority must be informed.

The trial or single dose steps will be terminated prematurely in the following cases:

- If adverse events occur which are so serious that the risk-benefit ratio is not acceptable.
- If the number of dropouts is so high that proper completion of the trial cannot realistically be expected.

# Methodology

## Screening investigation

All subjects, who are considered eligible for the participation in the present trial will undergo following procedures at the screening visit:

- Medical history

- Physical examination

- Vital signs (blood pressure, heart frequency), weight and height

- 12-lead ECG

## Dose selection, treatment duration and modification

CsA will be dosed as necessary to achieve 2h-CsA-serum concentrations of 500-1000 ng/dl.

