# 2 Protocol Synopsis

| TITLE | Hepatitis C in renal transplant recipients – The impact of cyclosporine A on HCV-replication, parameters of liver function and glucose tolerance | | | | | |
| --- | --- | --- | --- | --- | --- | --- |
| ACRONYM |  | | | | | |
| OBJECTIVES | **Primary Objective**   - To assess the impact of a conversion to a cyclosporine A-based immunosuppressive regimen on HCV-replication and parameters of liver function in renal transplant recipients   **Secondary Objectives**   - To assess the impact of a conversion to a cyclosporine A-based immunosuppressive regimen on parameters of insulin sensitivity and insulin secretion in renal transplant recipients | | | | | |
| DESIGN / PHASE | Prospective, mono-center, open, phase IV study. | | | | | |
| STUDY PLANNED DURATION | First patient  First visit | *3Q/*  *2011* | Last patient  **First visit** | *2Q/*  *2012* | **Last patient**  **Last visit** | *3Q/*  *2012* |
| CENTER(S) / COUNTRY(IES) | One center in one country.  Austria | | | | | |
| PATIENTS / GROUPS | 50 patients in one group | | | | | |
| INCLUSION CRITERIA | - .Written informed consent - .Prior renal transplantation with current immunosuppression other than cyclosporine A - Hepatitis C-infection - Age 18-70 years | | | | | |
| EXCLUSION CRITERIA | - Current hemodialysis or peritoneal dialysis - Pregnancy or breastfeeding - Known contraindications for / intolerability of calcineurin-inhibitors | | | | | |
| STUDY PERIODS |  | | | | | |
| INVESTIGATIONAL DRUG | **MED 1: Cyclosporine A**  initial dose: 10 mg/kg body weight/day  target dose: serum concentration 2 hours after administration 500-1000 ng/ml | | | | | |
| COMPARATIVE DRUG | Not applicable | | | | | |
| CONCOMITANT MEDICATION | **Allowed** | | | | | |
| EFFICACY ENDPOINTS | *HCV-RNA, l*iver transaminases, fibroScan-Indices, IL28-SNP, vitamin D, parameters of insulin sensitivity and insulin secretion, plasma adipokine levels | | | | | |
| TOLERABILITY / SAFETY ENDPOINTS | Glomerular filtration rate | | | | | |
| PHARMACOKINETIC / PHARMACODYNAMIC ENDPOINTS |  | | | | | |
| QUALITY OF LIFE / PHARMACOECONOMIC  ENDPOINTS |  | | | | | |

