# STUDY OBJECTIVES

## Primary Objective

The primary objective of the present study is to evaluate whether the conversion from a tacrolimus- to a CsA-based immunosuppression attenuates HCV-replication and other parameters of HCV disease activity at 2h-CsA-serum levels of 500-1000 ng/ml. Primary outcome parameter will be HCV-RNA and secondary parameters will be alanine transaminase (ALT), aspartate transaminase (AST) and gamma-glutamyltransferase (gGT).

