### Dosage and administration

*Substance Cyclosporine A*

*Dose,forms and strenghts :* 10 mg, 25 mg, 50 mg and 100 mg capsules

initial dose: 10 mg/kg body weight/day

maintenance dose: dose adjustment according to the 2h-CsA serum level (goal: 500-1000 ng/ml)

*Route:* oral

*Administration:* per os

*Study-drug lock diary:* measurement of 2h-CsA serum concentrations

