### Study-drug up- and down titration

Serum CsA levels will be measured 2 hours after the intake of CsA at each visit and if necessary for the achievement of target levels at additional timepoints. 2h-CsA goal levels will be 500-1000 ng/ml in all study participants independent of the time duration since renal transplantation to ensure CsA-serum concentrations previously shown to suppress HCV-replication *in vitro*.

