## Study procedures

### Description of study procedures

*7.4.1.1. Switch of immunosuppression*

Serum CsA levels will be measured 2 hours after the intake of CsA at each visit and if necessary for the achievement of target levels at additional timepoints. 2h-CsA goal levels will be 500-1000 ng/ml. In addition, parameters of renal function including serum creatinine and protein excretion in 24h-urine will be determined every four weeks during the study period according to local standards of routine care.

*7.4.1.2. Evaluation of liver function*

*7.4.1.2.1. Transient elastography*

Parameters of liver stiffness will be assessed by transient elastography (FibroScan®, Echosens, Paris France), as described previously [49]. Transient elastography represents a novel approach for staging of hepatic fibrosis and has been tested in multiple study collectives with varying degrees of liver fibrosis and cirrhosis including subjects with hepatitis C. This technique rapidly and non-invasively measures the mean hepatic stiffness by means of an ultrasonic transducer, which transmits a vibration of low frequency (50 Mhz) and amplitude into the liver. The vibration wave induces an elastic shear wave that propagates through the liver tissue. The velocity of this wave as it passes through the liver correlates directly with tissue stiffness. The harder or stiffer the tissue, the faster the shear wave propagates.

All measurements will be performed on the right lobe of the liver through intercostal spaces on patients lying in the dorsal decubitus position with the right arm in maximal abduction. The tip of the transducer probe will be placed in an intercostal space at the level of the right lobe of the liver. A liver portion of 6 cm thickness free of large vascular structures will be located before the measurement will be started by pressing the probe button. The results will be expressed in kilopascal (kPa) and the median value considered representative of the liver stiffness. Only procedures with 10 valid measurements, a success rate (= ratio of the number of successful measurements over the total number of acquisitions) ≥ 80% and an interquartile range (IQR) < 10 kPa will be considered reliable. Time expenditure for the assessment of liver stiffness by transient elastography is estimated at 5 minutes per patient.

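### Section 7.2 gives the 2-hour cyclosporine target in ng/dl and five other places give it in ng/ml: a 100-fold contradiction in the exposure that guides dosing and is named in the primary objective

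*Protocol*

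**What the plan says.** The protocol states the target for the serum cyclosporine A (CsA) concentration 2 hours after intake in six places.

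- Section 7.2, Dose selection, treatment duration and modification: "CsA will be dosed as necessary to achieve 2h-CsA-serum concentrations of 500-1000 ng/dl". This sentence is the whole section.
- Section 2, Protocol Synopsis: "target dose: serum concentration 2 hours after administration 500-1000 ng/ml".
- Section 5.1, Primary Objective: the effect of conversion is to be evaluated "at 2h-CsA-serum levels of 500-1000 ng/ml".
- Section 7.3.1, Dosage and administration, for the maintenance dose: "dose adjustment according to the 2h-CsA serum level (goal: 500-1000 ng/ml".
- Section 7.3.2, Study-drug up- and down titration: "2h-CsA goal levels will be 500-1000 ng/ml in all study participants independent of the time duration since renal transplantation".
- Section 7.4.1.1, Switch of immunosuppression: "2h-CsA goal levels will be 500-1000 ng/ml".

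The table of biochemical measurements lists 2-hour CsA levels at weeks 4, 8 and 12 but gives no unit for them.

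**The concern.** The numerals agree in all six places, but the unit in Section 7.2 does not. The figure is not background text. It is the quantity to which the dose is adjusted, and Section 5.1 makes it part of the question the trial asks. Section 7.3.2 justifies it by reference to concentrations that suppress HCV replication in vitro.

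The location makes it worse. A reader looking for the dosing rule would go to the section headed dose selection and modification. There they find only the ng/dl figure, with no cross-reference to Sections 7.3.1 or 7.3.2. The protocol does not say which section prevails when two disagree.

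Two things are at stake. One is an unambiguous dosing instruction for a drug class that Section 4.1.1 describes as part of the lifelong treatment needed to prevent rejection. The other is a single definition of the exposure to which the primary result refers.

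**Working it through.** The target is a fixed specification with no formula behind it, so the check is a unit conversion and a comparison of every statement of the target.

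**Conversion.** 1 dl = 100 ml, so x ng/dl = x/100 ng/ml.

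- Lower limit in Section 7.2: 500 ng/dl = 500/100 = 5 ng/ml.
- Upper limit in Section 7.2: 1000 ng/dl = 1000/100 = 10 ng/ml.
- Conversely, 500-1000 ng/ml = 50,000-100,000 ng/dl.

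**Side by side, in one unit.**

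| Place | As written | In ng/ml |
| --- | --- | --- |
| 7.2 Dose selection | 500-1000 ng/dl | 5-10 |
| 2 Synopsis | 500-1000 ng/ml | 500-1000 |
| 5.1 Primary Objective | 500-1000 ng/ml | 500-1000 |
| 7.3.1 Dosage and administration | 500-1000 ng/ml | 500-1000 |
| 7.3.2 Titration | 500-1000 ng/ml | 500-1000 |
| 7.4.1.1 Switch | 500-1000 ng/ml | 500-1000 |

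**Size of the gap.** Corresponding limits differ by 500/5 = 1000/10 = 100. Even the nearest edges are far apart: the top of the Section 7.2 range is 10 ng/ml and the bottom of the other range is 500 ng/ml, a ratio of 500/10 = 50. The ranges share no value, so any level on target under one statement is off target under the other.

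**Does it reach the statistics?** The planned size was recomputed with the exact paired t-test (difference 1, SD of differences 1.5, two-sided 5%).

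- The noncentrality parameter for n = 26 is (1/1.5) × √26 = 3.40.
- Power is 90.4%, against the stated 90%.
- Allowing for 10% drop-out, 26/(1 − 0.10) = 28.9, so 29, against the stated figure of about 30.

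The plan's own figures reproduce, and the CsA target enters none of them. Section 10.4.1 specifies a paired t-test on log10 HCV-RNA at 12 weeks and does not condition on the CsA level.

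**The case against.** The strongest reply is that this is a slip in one unit and not a second regimen. Sections 7.3.1, 7.3.2 and 7.4.1.1, which carry the working instructions, agree with each other, with the synopsis and with the primary objective. The background in Section 4.1.3 also reports an in vitro CsA concentration in ng/ml. The trial runs at a single centre on that clinic's own routine-care patients, and nothing in the protocol suggests that anyone would titrate to the Section 7.2 figure.

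Most of this stands as an account of how the discrepancy probably arose, and it limits the practical ambiguity. It does not remove the contradiction. The discrepant line is the entire content of the dose-selection section, and the reader should not have to infer the intended unit by counting statements.

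Some stronger readings are tempting but unsupported:

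- **Higher nephrotoxicity risk.** The discrepant value is the lower one, so following it would mean less CsA exposure. The documents give no route from the conflict to more nephrotoxicity.
- **A broken deviation criterion.** There is none for CsA levels. Section 10.3 says only that deviations will be listed, and Section 10.1 refers to major violations without naming a CsA threshold.
- **A 100-fold dosing error in patients, or in every titration decision.** The factor of 100 lies between two written ranges. Section 7.3.2 is clear within itself and agrees with the primary objective.

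**Conclusion.** The contradiction is real and follows from the text alone. Section 7.2 sets 5-10 ng/ml where five other places set 500-1000 ng/ml, a factor of exactly 100 with no overlap. The sentence in Section 7.2 is intact running prose in the current protocol, with no sign of a redaction or a broken table. The only assumption is the standard conversion of decilitres to millilitres.

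The finding is limited to the specification of dosing and exposure: the dose-selection section disagrees with the titration rule and with the primary objective. The objective and the titration rule agree with each other, and the sample size and primary test are unaffected. The point still warrants correction before treatment starts, because the figure is an operative target for the study drug. This review takes no view on which range is clinically right; the sponsor must confirm that.

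**What to change.** The sponsor should confirm the intended unit and reconcile Section 7.2 with the Synopsis and Sections 5.1, 7.3.1, 7.3.2 and 7.4.1.1 before the first conversion. The confirmed unit should then appear wherever 2-hour CsA levels are recorded, including the table of biochemical measurements, and wherever adherence to the target is judged, for example when the per-protocol set is formed. The case report form is not shown, so its unit should be checked.

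The cost is small: one unit changed in Section 7.2 if that line is the one in error, or the other five statements if it is not. Either way the change goes through the amendment procedure in Section 12.2.1.1. No recalculation of the sample size and no change to the analysis is needed.

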## Study medication

Since only accredited preparations are being used and since the national health insurances are defraying for all medication costs; there are no special precautions to regard referring to medication management that are differing from standard storage in daily clinical routine. All medication is not blinded and used according to the Summary of Product characteristics.

Active agent and it´s characteristics: Cyclosporine A

Trade name of the agent: Sandimmun ®

Manufacturer: Novartis GmBH

Drug supply: Local pharmacy, i.e. external drugstore

Storage Instructions: Room temperature

Packing instructions: Cyclosporine A will obtained as Sandimmun ® in its trading package from local pharmacies, i.e. external drugstores.

Route of administration: per os

Referring to a reference point (product characteristics…)

### Dosage and administration

*Substance Cyclosporine A*

*Dose,forms and strenghts :* 10 mg, 25 mg, 50 mg and 100 mg capsules

initial dose: 10 mg/kg body weight/day

maintenance dose: dose adjustment according to the 2h-CsA serum level (goal: 500-1000 ng/ml)

*Route:* oral

*Administration:* per os

*Study-drug lock diary:* measurement of 2h-CsA serum concentrations

### Study-drug up- and down titration

Serum CsA levels will be measured 2 hours after the intake of CsA at each visit and if necessary for the achievement of target levels at additional timepoints. 2h-CsA goal levels will be 500-1000 ng/ml in all study participants independent of the time duration since renal transplantation to ensure CsA-serum concentrations previously shown to suppress HCV-replication *in vitro*.

### Study drug interruption or discontinuation

The investigator must temporarily interrupt or permanently discontinue the study drug if continued administration of the study drug is believed to be contrary to the best interests of the patient.

The interruption or premature discontinuation of study drug might be triggered by an AE, a diagnostic or therapeutic procedure, an abnormal assessment (e.g., laboratory abnormalities), or for administrative reasons, in particular withdrawal of the patient’s consent.

The reason for study drug interruption or premature permanent discontinuation must be documented in the CRF.

If the reason for premature permanent discontinuation of study treatment is an AE, the patient should have a “Premature EOS” visit with all the assessments performed before the study drug discontinuation, whenever possible.

If the reason for premature permanent discontinuation of study treatment is not an AE, the patient should be withdrawn from the study (withdrawal of consent) and have the EOS visit with all the assessments performed before the study drug discontinuation, whenever possible.

### Study-drug delivery & drug storage conditions

Since only accredited preparations are being used and since the national health insurances are defraying for all medication costs; there are no special precautions to regard referring to medication management that are differing from standard storage in daily clinical routine. Patients will be advised to store the drugs as recommended by the producer at room temperature.

### Study drug packaging and labeling

Study medication is used according to the summary of Product Characteristics. No special requirements for labeling are thus foreseen..

### IMP administration & handling

Administration and Handling will be done according to the SmPC.

### Drug Accountability

Drug Accountability will be recorded at on-going basis on paper form/source data and the date of drug dispensing by local, external pharmacies entered in the CRF at each visit. Furthermore the correct intake of IMP or any variations concerning that will be recorded in the CRF at each visit during treatment period.

Cyclosporine A will be prescribed as Sandimmun ® (trade name) in trading packages à 50 tablets, which will be obtained from local pharmacies, i.e. external drugstores, by the study participants themselves. All study participants will be asked to keep the used (empty) drug blisters and to return them to the study site for drug accountability. Drug accountability check will be performed at each visit.

### Concomitant medication

The well-being of the patient has the first priority, and modifications of concomitant treatment during the trial are allowed as necessary and will be documented in the patient’s records.

In this study, all concomitant medications are allowed, with the exception of:

Not allowed: HCV-specific antiviral therapy

### Interactions, reverse reactions and side effect of IMP:

*Cyclosporin A – interactions*

(according to http://medis.akhwien.at/cgi-bin/medisweb.exe?app_fach%20120689)

Caution when used with other nephrotoxic substances, e.g. aminoglycosides, amphotericin B, ciprofloxacin, melphalan, colchicine, trimethoprim, vancomycin, non-steroidal antiphlogistics, H2-receptor antagonists, methotrexate, lercarnidipine,...

Increase of cyclosporin A-serum concentrations by e.g., amphotericin B, keto-, flu-, itra- and voriconazole, erythro-, josa- and clarithromycin, doxycycline, oral contraceptives, propafenone, calcium-antagonists, metoclopramide, danazole, methylprednisolone, allopurinole, amiodarone, cholic acid, protease-inhibitors, imatinib, colchicine, nefazadone, ...

Decrease of cyclosporine A-serum concentrations by e.g., barbiturates, carbamazepine, oxcarbazepine, phenytoine, metamizole, rifampicin, nafcillin, sulfadimidine intravenous, trimethoprim, octreotide, probucol, orlistat, hypericum perforatum, ticlopidine, sulfinpyrazone, terbinafine, bosentan, ...

*Cyclosporin A – side effects*

(according to http://medis.akhwien.at/cgi-bin/medisweb.exe?app_fach%20120689)

| **system** | **frequency** |  |
| --- | --- | --- |
| *blood, lymph system* | >1/1000, <1/100 | anemia, thrombocytopenia |
|  | >1/10000, <1/1000 | leukopenia, microangiopathic hemolytic anemia, hemolytic-uremic syndrome |
|  | >1/1000, <1/100 | menstruation dysorders |
|  | >1/10000, <1/1000 | hyperthermia, gynaecomastia, hot flushes |
| *metabolism* | >1/10 | hyperlipidemia |
|  | >1/100, <1/10 | anorexia, hyperuricemia |
|  | >1/1000, <1/100 | hyperkalemia, hypomagnesemia, weight gain, hyperglycemia |
| *nervous system* | >1/10 | tremor, head ache |
|  | >1/100, <1/10 | fatigue, parasthesia |
|  | >1/1000, <1/100 | signs of encephalopathy (e.g. convulsions, desorientation, sleeping disorders) |
|  | >1/10000, <1/1000 | motoric polyneuropathy |
|  | <1/1000 | deafness, papillary edema |
| *cardiovascular* | >1/10 | hypertension |
|  | >1/100, <1/10 | ischemic heart disease |
| *gastrointestinal* | >1/100, <1/10 | gingivitis hypertrophicans, gastrointestinal symptoms |
|  | >1/1000, <1/100 | gastric ulcera |
|  | >1/10000, <1/1000 | pancreatitis |
|  | <1/1000 | colitis |
| *liver, bile* | >1/1000, <1/100 | reversible increase of bilirubin and parameters of liver function |
| *skin* | >1/100, <1/10 | hypertrichosis |
|  | >1/1000, <1/100 | acne, rash |
|  | >1/10000, <1/1000 | redness, pruritus |
| *musculo-skeletal* | >1/100, <1/10 | seizures, muscle pain |
|  | >1/10000, <1/1000 | myopathy, weakness |
| *kidney, urinary tract* | >1/10 | increase of serum creatinine |

### Randomization and stratification:

Not applicable

### Blinding

Not applicable

**7.3.12. Benefit and risk assessment**

Benefits

- Reduction of HCV-replication and improvement of liver function with consecutive improvement of quality of life and reduced HCV-associated morbidity and mortality

Risks:

- Potential increase of serum creatinine after conversion, which however is anticipated to be reversible. In case of a significant decrease of graft function, defined as 50% reduction of the glomerular filtration rate (GFR) in subjects with a GFR ≥50 ml/min at baseline and as 30% reduction of the GFR in subjects with a GFR <50 ml/min at baseline, the study drug will be discontinued in the respective study participant and immunosuppression re-converted to a tacrolimus-based regimen.

In case of serious side effects or serious other medical safety concerns, single study participants will be withdrawn or the whole study prematurely terminated; the immunosuppression will be re-converted to a tacrolimus-based regimen.

